## Abstract

Sleep deficiency is a hidden cost of our 24–7 society, with 70% of adults in the US admitting that they routinely obtain insufficient sleep. Further, it is estimated that 50–70 million adults in the US have a sleep disorder. Undiagnosed and untreated sleep disorders are associated with diminished health for the individual and increased costs for the employer. Research has shown that adverse impacts on employees and employers can be mitigated through sleep health education and sleep disorder screening and treatment programs. Smartphone applications (app) are increasingly commonplace and represent promising, scalable modalities for such programs. The dayzz app is a personalized sleep training program that incorporates assessment of sleep disorders and offers a personalized comprehensive sleep improvement solution. Using a sample of day workers affiliated with a large institution of higher education, we will conduct a single-site, parallel-group, randomized, waitlist control trial. Participants will be randomly assigned to either use the dayzz app throughout the study or receive the dayzz app at the end of the study. We will collect data on feasibility and acceptability of the dayzz app; employee sleep, including sleep behavioral changes, sleep duration, regularity, and quality; employee presenteeism, absenteeism, and performance; employee mood; adverse and safety outcomes; and healthcare utilization on a monthly basis throughout the study, as well as collect more granular daily data from the employee during pre-specified intervals. Our results will illuminate whether a personalized smartphone app is a viable approach for improving employee sleep, health, and productivity.

**Trial registration**: ClinicalTrials.gov Identifier: NCT04224285.

## Introduction

Sleep deficiency is a hidden cost of our 24–7 society, with 70% of Americans admitting they routinely obtain insufficient sleep [1]. The issue is pervasive in our workforce, as 30% of United States (US) workers report sleeping less than 6 hours per night [2]. Additionally, approximately 50–70 million individuals in the US have a sleep disorder [3]. Undiagnosed and untreated sleep disorders are associated with short and long-term health consequences for the individual and generate substantial direct and indirect costs for the employer.

Diminished alertness as a result of sleep deficiency or undiagnosed and untreated sleep disorders are associated with increased costs to employers. Costs attributable to sleep deficiency in the US were estimated to exceed $410 billion dollars in 2015, equivalent to 2.28% of the gross domestic product [4]. Despite the importance of healthy sleep for workplace productivity and employee health and safety, nationally representative survey data collected from employers in the US shows that fewer than 10% of worksites report offering sleep-focused programs [5].

Sleep disorders are very common, with 30–40% of employees screening positive for at least one common sleep disorder [6–9]. Approximately 85% of those with sleep disorders are undiagnosed and untreated [6,10]. Screening positive for a sleep disorder has been associated with a myriad of adverse health consequences, including increased risk of cardiovascular disease, diabetes and depression [6,10]. Sleep disorders also compromise safety, being associated with an increased risk of motor vehicle crashes [10] and administrative errors or safety violations [6]. Further, research has shown that hospital workers who screened positive for a sleep disorder had an 83% increased incidence of adverse safety outcomes (including medical errors, needlestick injuries, and motor vehicle crashes) over a 6-month interval [9].

Research has shown that workplace health programs focused on employee sleep or sleep disorders screening are effective for improving employee sleep, health, well-being, and workplace outcomes. In a randomized controlled trial of an in-person sleep education and sleep disorders screening intervention, researchers found there was a 24% reduction in injuries and a 46% reduction in disability day usage over the following year [10]. In a national trucking company, each employee diagnosed and treated for sleep apnea through an employer-sponsored program, saved nearly $3,000 per employee in health care costs annually [11].

In part catalyzed by the COVID-19 pandemic, there has been a widespread adoption of flexible and work-from-home policies among employers [12], and many forecast that worksites are likely to feature these policies when employees return to work [13]. These trends present new challenges to employee health and wellbeing when employees manage both work and personal obligations inside the home. The trend toward increased work-from-home policies and flexible work schedules may also presents opportunities for digital health programs for improving employee health. Digital platforms, such as websites, virtual coaching, and smartphone applications, may extend sleep health and wellness programs and offer tangible benefits to employers, such as scalability and cost effectiveness. These digital and mobile health (mHealth) approaches are particularly promising as they have the ability to monitor user behavior (e.g., time spent sleeping or number of steps taken) and to personalize messages tailored to a user’s lifestyle and needs [14,15], aimed at nudging towards health promoting behaviors and attitudes.

The purpose of this study is to conduct a randomized controlled trial to evaluate a smartphone app designed to improve employee sleep health and improve workplace outcomes. We will ascertain the feasibility and acceptability of the smartphone app and determine whether use of the app will improve sleep, health, mood, productivity, safety, and productivity among a large employee population in the US Northeast.

## Materials and methods

### Study design

We will conduct a single-site, randomized, two-arm, parallel-group controlled trial using a waitlist control design. We will enroll a target of 1,000 daytime employees into the study, 500 randomly assigned to the experimental group and 500 to the control group. The experimental group will receive access to the dayzz app as well as to a short sleep health and wellness (SHAW) education program, developed by the Sleep Matters Initiative which includes screening for common sleep disorders. The control group will receive the dayzz app and SHAW at the end of the study. The study recruitment was originally intended to be conducted in-person. However, due to the onset of the COVID-19 pandemic at the start of study implementation, the study recruitment, enrollment, and follow-up procedures were re-designed to be completed entirely online. Please see the Fig 1 for a flowchart of enrollment, interventions, and assessments.

**Fig 1 pone.0260828.g001:**
[figure not shown]
SPIRIT flowchart of the schedule of enrolment, interventions, and assessments.

### Participants

Eligible participants will be daytime workers employed by a large research and teaching organization in the US Northeast. Participants must be employed by the organization, work during the daytime, own and use a smartphone, and regularly use smartphone apps (i.e., once per week). Exclusion criteria for this study are regularly working evening, night or rotating shifts and pregnancy or breast-feeding.

### Recruitment and retention

Recruitment will include two emails that will be sent to more than 20,000 members of the organization with an invitation to visit the study website for more information. An advertisement for the study will also be posted on a website hosted by the organization that is devoted to research and study recruitment, with a wide circulation (>10,000 visitors monthly). Finally, will post targeted social media advertisements to individuals who report the organization as their primary employer on Facebook and LinkedIn.

Potential participants will be directed to an online landing page with more information about the study. An online screener will be automatically scored and used to determine eligibility according to the study inclusion/exclusion criteria, resulting in either an invitation to provide consent and complete the baseline procedure, or a message indicating they were not eligible. Due to the virtual nature of this study, consent was collected via electronic signature. Participants were informed they could stop at any time, and who had questions were encouraged to email or call the study team. Participant responses will be de-identified and results published in aggregate. No identifiable data will be disclosed to the employer.

After providing consent via the online landing page, participants were automatically randomized by a computer program. Due to the multiple steps necessary to enroll in the experimental arm, we weighted assignment to the experimental group 1.3 to 1 to ensure equal enrollment in each group.

All enrolled participants will receive $25 for completing the baseline procedures, a t-shirt ($10 value) for completing the first monthly sleep diary, and a $20 gift card for completing the end-of-study questionnaire. Each month, participants who complete the monthly questionnaire which they receive via email will be entered in a raffle to win one of two pairs of Bluetooth wireless headphones ($250 value each). Finally, for each study component completed, participants receive chances for a raffle of gift cards, ranging in value from $100 to $500, at the end of the study. Participants who are unresponsive to emailed questionnaires will receive up to 2 reminder follow-up emails.

### Study arms

#### Experimental arm

After consenting, participants randomized to the experimental group will take a short online initial contact questionnaire to collect basic demographics. They will then view a 20-minute sleep health education video. Immediately after the presentation, the participant will be presented with a short sleep disorders risk assessment which displays the results upon completion, either high risk for a sleep disorder (obstructive sleep apnea, insomnia, or restless legs syndrome) or low/no risk a sleep disorder. Participants are then presented with a baseline questionnaire to assess sleep, health, and lifestyle. Finally, the experimental group participants will be invited to download the study app (“dayzz”). They will be encouraged to use the dayzz app throughout the study (up to 9 months, depending on date of enrollment).

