#### Control

Participants assigned to the waitlist control condition will, at baseline, complete the same initial contact and baseline questionnaires. Participants in the waitlist control group will complete the eDiary and monthly and end-of-study questionnaires. At the end of the study, waitlist control participants will receive the intervention (SHAW and dayzz app).

Each participant will also complete a daily electronic sleep diary (eDiary) sent via email for one week within the first month of enrollment and for one week within the third month of the study. For up to 9 months following the baseline procedure, on the 28th of each month, each participant will receive an email with a link to the monthly questionnaire. At the end of the study, each participant will receive a link to complete the end-of-study questionnaire. The eDiary and all questionnaires are completed online. This study was approved by the Partners HealthCare Institutional Review Board (IRB) on February 10, 2020 (Protocol #: 2019P003277). Please see the Fig 2 for a flow chart describing the study procedures. Per the IRB, a Data Safety Monitoring Board was not required for this clinical trial.

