### Statistical plan

We plan to analyze anonymized data using an intention-to-treat approach (ITT). All outcome measures will be compared by assignment to the experimental and waitlist control groups in the primary analysis. The primary ITT analysis will include all participants who are randomized in the study. Secondary analyses will compare outcomes using an as-treated approach and an adherent to treatment approach. The as-treated approach will compare those who download dayzz to those who do not, regardless of their assigned randomization. We anticipate some cross-over between groups due to sharing of the app information among study participants. The adherent to treatment approach will exclude participants from the experimental group who did not engage with app throughout the study. We further plan to quantify temporal changes within participants assigned to the experimental group.

To evaluate changes in sleep behavior, we will examine the distribution of the data to determine if it meets assumptions for parametric tests. Assuming randomization has balanced known and unknown confounders and we observe a normal distribution, we will compare sleep duration between the groups using a t-test. We will use a rank sum test if the distribution is not normal. The distribution of the data will be examined, and transformations will be performed as necessary for valid comparisons. If potential confounders are not balanced between groups, we plan to use regression models with an appropriate link function and distribution to test all hypotheses. The number of healthy sleep changes at the end of the study will be compared between the groups using a rank sum test.

To evaluate changes in sleep quality, we will compare the proportion of participants with poor sleep quality according to the PSQI in the experimental group versus the waitlist control group using a chi-2 test. These continuous measures will be compared using a t-test. To examine changes in mood, alertness, and energy we will compare these ordinal variables using Wilcoxon rank sum tests between the experimental and waitlist control arms. We will estimate changes in absences and productivity using reported salary information and compare the cumulative cost of each using a t-test. We will estimate the incidence of crashes, near-crashes, and injuries which will then be compared using Poisson regression. Finally, we will compare cumulative healthcare costs over the study using t-tests.

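### The experimental arm completes its baseline questionnaire after the sleep video and risk result, so imbalance-triggered adjustment for its self-rated items can bias the effect

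*Protocol article*

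**What the plan says.** The order of events can be read from three sections of the Protocol article.

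- Recruitment and retention: "After providing consent via the online landing page, participants were automatically randomized by a computer program". Randomisation therefore precedes every questionnaire.
- Experimental arm: "participants randomized to the experimental group will take a short online initial contact questionnaire to collect basic demographics". Next, "They will then view a 20-minute sleep health education video". Then "the participant will be presented with a short sleep disorders risk assessment which displays the results upon completion". Only after these steps: "Participants are then presented with a baseline questionnaire to assess sleep, health, and lifestyle". The invitation to download the app comes last.
- Control: these participants "complete the same initial contact and baseline questionnaires". No video or risk result is described for them at this stage; they receive the education programme (SHAW) and the app at the end of the study.

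Study design makes SHAW, including its screening, part of what the experimental group receives. The Statistical plan compares the arms without adjustment by default, but adds a condition: "If potential confounders are not balanced between groups, we plan to use regression models", and these models are to test all hypotheses. It also plans to quantify temporal changes within the experimental arm. Power analysis gives 0.16 as the detectable effect size with 500 per group.

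**The concern.** A baseline covariate is safe to adjust for because treatment cannot have changed it. That does not hold here for self-rated items. Someone who has just been taught about healthy sleep, and told whether they are at high or low risk of a sleep disorder, may rate their sleep, health or habits differently from someone who has not. If so, the arms differ on the questionnaire because of the intervention.

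The adjustment rule could read that difference as a chance imbalance, switch to regression and adjust for a consequence of treatment. Nothing in the rule limits covariates to items collected before the video. The error could go either way: heightened awareness could make recorded sleep look worse in the experimental arm and inflate the adjusted benefit, or the ratings could move the other way and shrink it. Within-arm change measured from this questionnaire would also start from a value already touched by part of the intervention.

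**Working it through.** **1. Order of events, side by side**

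| Step after randomisation | Experimental | Control |
|---|---|---|
| Initial contact questionnaire (demographics) | yes | yes |
| Education video | yes | not until study end |
| Risk assessment with result shown | yes | not described at baseline |
| Baseline questionnaire (sleep, health, lifestyle) | after the two steps above | without them |

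Figure 2 is not available to this review; nothing in the text contradicts this order.

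**2. The yardstick.** The plan's 0.16 is used only for scale. Its alpha, sidedness and power are not stated. Detectable d = (z_alpha + z_power) × √(2/500), where √(2/500) = 0.0632.
- One-sided 5%, 80% power: (1.645 + 0.842) × 0.0632 = 0.157, which rounds to 0.16.
- Two-sided 5%, 80% power: (1.960 + 0.842) × 0.0632 = 0.177.

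**3. Bias of the adjusted estimate.** Let δ be the shift in the experimental arm's recorded baseline (in SD), ρ the baseline-outcome correlation and τ the true effect. Suppose the shift does not carry over to follow-up.
- Unadjusted difference: expectation τ, so no bias.
- Adjusted difference: expectation τ − ρδ, so bias −ρδ.

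Neither δ nor ρ is in the documents. Assumed ranges are δ = 0.05 to 0.2 and ρ = 0.3 to 0.7.
- Low: 0.3 × 0.05 = 0.015; 0.015/0.16 = 9%.
- Middle: 0.5 × 0.1 = 0.05; 0.05/0.16 = 31%.
- High: 0.7 × 0.2 = 0.14; 0.14/0.16 = 88%.

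**4. The trigger.** The plan does not define imbalance. As an assumption, regression was used when the baseline difference had two-sided p < 0.05. Simulation used 500 per arm, 4,000 trials per setting, τ = 0 and two-sided 5% tests. Each cell gives mean bias in SD / type I error.

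| δ | ρ | Trigger fires | Unadjusted | Always adjusted | Triggered procedure |
|---|---|---|---|---|---|
| 0 | 0.5 | 5.3% | 0.000 / 5.1% | −0.001 / 4.6% | 0.000 / 4.3% |
| 0.05 | 0.3 | 12.2% | −0.002 / 4.9% | −0.016 / 5.6% | −0.007 / 4.6% |
| 0.1 | 0.5 | 34.5% | −0.002 / 4.8% | −0.052 / 16.0% | −0.031 / 8.1% |
| 0.2 | 0.5 | 88.0% | 0.000 / 4.7% | −0.099 / 43.5% | −0.093 / 39.8% |
| 0.2 | 0.7 | 89.0% | 0.002 / 4.9% | −0.139 / 86.3% | −0.132 / 78.3% |

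The shift makes the trigger fire more often, and when it fires the adjusted estimate carries the bias −ρδ (−0.050 at δ = 0.1, ρ = 0.5). With δ = 0, which is what measuring before the video secures, there is no bias.

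**5. With a true effect of 0.16** and ρ = 0.5, δ = +0.1 moves the always-adjusted estimate to 0.110 and δ = −0.1 moves it to 0.210. The triggered procedure averages 0.131 and 0.190.

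**6. If the shift persists in full to follow-up reports**, the unadjusted expectation becomes τ + δ and the adjusted one τ + δ − ρδ. Adjustment then removes part of the distortion. The result in step 3 therefore depends on the shift fading.

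**The case against.** The strongest reply is that the planned between-arm tests (t, rank sum, chi-square, Poisson) compare the arms without using baseline. Even the sleep-quality analysis, although described as evaluating change, compares the proportion of poor sleepers between arms. This stands: used on their own, those comparisons are unbiased by the ordering, as the unadjusted column shows.

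It is also fair that bias from adjustment needs three things together: the trigger fires, a self-rated item from this questionnaire is chosen, and the video or risk result has changed the answer. The plan refers to potential confounders without naming sleep ratings. Demographics precede the video, fixed history should barely move, and a covariate list is commonly left to an analysis plan that is not shown. This makes the harm conditional. An analysis plan could restrict the covariates, but it could not recover a pre-video rating.

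The size is wholly assumed, and at the low end the triggered procedure is almost harmless (bias 0.007 SD, type I error 4.6%). That also stands.

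Three stronger readings are tempting, and the documents do not support them.
- A reader might infer that the main intention-to-treat comparison is biased. By default it uses no baseline.
- A reader might infer a between-arm change-score analysis biased by the full shift. None is planned; the only explicit change analysis is within the experimental arm.
- A reader might infer that the first eDiary week is a mislabelled baseline. The text places it "for one week within the first month of enrollment" and never calls it a baseline. It simply cannot stand in for a pre-video measure.

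**Conclusion.** The sequencing weakness is real and clear from the text: self-rated items in the baseline questionnaire are post-intervention in the experimental arm only. The consequence is a conditional risk to two analyses, the imbalance-triggered regression and, if it starts from this questionnaire, the within-arm temporal analysis. It is correct to say that the adjustment can bias the effect; the documents do not establish that it would.

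Under the assumed shift (0.05 to 0.2 SD), correlation (0.3 to 0.7) and no persistence to follow-up, an adjusted estimate is off by about 0.015 to 0.14 SD, or 9% to 88% of 0.16, in an unknown direction. In the middle case (0.1 SD, 0.5) the whole triggered procedure has bias 0.031 SD and type I error 8.1%, given the assumed p < 0.05 trigger. Confidence is high for the ordering and low for the size. The point merits correction because the remedy is cheap; it does not invalidate the default comparisons.

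**What to change.** - **Participants not yet enrolled:** place the baseline questionnaire before the video and risk assessment in the experimental arm, ideally before randomisation in both arms. The procedures are already online, so this reorders existing pages.
- **Participants already enrolled** (the Discussion dates the launch to August 2020): limit balance checks and regression covariates to items collected before the video (basic demographics) or to fixed history items.
- **Temporal analysis in the experimental arm:** do not treat self-rated items from this questionnaire as an untreated starting point, and say so when reporting.

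The cost is some precision, because self-rated baseline sleep is no longer available as a covariate for those already enrolled. A change after launch also creates two baseline orderings, so the version each participant received should be recorded.

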#### Control

Participants assigned to the waitlist control condition will, at baseline, complete the same initial contact and baseline questionnaires. Participants in the waitlist control group will complete the eDiary and monthly and end-of-study questionnaires. At the end of the study, waitlist control participants will receive the intervention (SHAW and dayzz app).

Each participant will also complete a daily electronic sleep diary (eDiary) sent via email for one week within the first month of enrollment and for one week within the third month of the study. For up to 9 months following the baseline procedure, on the 28th of each month, each participant will receive an email with a link to the monthly questionnaire. At the end of the study, each participant will receive a link to complete the end-of-study questionnaire. The eDiary and all questionnaires are completed online. This study was approved by the Partners HealthCare Institutional Review Board (IRB) on February 10, 2020 (Protocol #: 2019P003277). Please see the Fig 2 for a flow chart describing the study procedures. Per the IRB, a Data Safety Monitoring Board was not required for this clinical trial.

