#### Changes in sleep behavior

We will evaluate changes in sleep behaviors on the monthly and the end-of-study surveys. Using a checklist, participants will be asked to select the healthy sleep changes they have made since starting the study. Specifically, participants are asked “During this study, have you changed any sleep-related behaviors to improve your sleep since participating in the study (check all that apply)?” Participants have the option to select changes they may have made, such as “Go to bed earlier,” “Keep a more consistent sleeping schedule,” and “Set an alarm to remind you of your bedtime.” Participants are also able to select “other” and identify the healthy sleep change they made since joining the study.

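### The rank sum test on the end-of-study checklist count ignores time on study, which varies with enrolment date; stratifying by enrolment month is an optional, near-free gain in precision

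*Protocol article*

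**What the plan says.** All references are to the Protocol article.

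- **Time on study varies.** Experimental arm, on app use: "They will be encouraged to use the dayzz app throughout the study (up to 9 months, depending on date of enrollment". Control, on the monthly forms: "For up to 9 months following the baseline procedure, on the 28th of each month, each participant will receive an email".
- **The closing form is tied to study end.** Control: "At the end of the study, each participant will receive a link to complete the end-of-study questionnaire". No time since randomisation is set for it. That study end is one calendar date for everyone is an inference from the dependence on enrolment date, but a strong one.
- **The outcome is cumulative.** Changes in sleep behavior: participants "select the healthy sleep changes they have made since starting the study". The same section says "We will evaluate changes in sleep behaviors on the monthly and the end-of-study surveys".
- **The test.** Statistical plan: "The number of healthy sleep changes at the end of the study will be compared between the groups using a rank sum test".
- **The fallback.** Statistical plan: "If potential confounders are not balanced between groups, we plan to use regression models".

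**The concern.** A checklist of changes made since joining can lengthen the longer a person has been in the study. The planned test ranks a recent enrolee together with someone who has had 9 months, as though both were seen at the same point. Part of the spread in ranks may then reflect enrolment date, which is known for each participant and unrelated to arm. Leaving it in the error term costs power on the only test named for the checklist count.

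The regression fallback does not normally help. It applies when potential confounders are unbalanced, whereas randomisation should balance enrolment date. A factor can be balanced between arms and still add noise.

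**Working it through.** **Inputs from the article:** 500 per arm; time on study up to 9 months; unstratified rank sum test. **Assumed, because not stated:** minimum time on study (1, 3 or 6 months), uniform enrolment, two-sided 5% level, growth of the count over time, and an experimental rate or mean 15% higher.

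**1. The plan's own figure.** The Power analysis gives a detectable effect size of 0.16. With one-sided 5% and 80% power (assumed), (1.645 + 0.842) × √(2/500) = 2.487 × 0.0632 = 0.157, which rounds to 0.16. Two-sided gives 2.802 × 0.0632 = 0.177. Neither contains time on study, so the figure does not settle this point.

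**2. How much variance is time on study?** Take a control-arm count with mean 3 at month 6, growing linearly (mean t/2), with gamma-Poisson dispersion 0.3. For t uniform on 3 to 9:
- variance of the mean due to time: (1/4) × 6²/12 = 0.75
- variance at a given time: 3 + 0.3 × (3² + 0.75) = 5.925
- share due to time: 0.75 / 6.675 = 11%

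The same steps give 0.1875 / 8.2125 = 2% for 6 to 9 months and 1.333 / 6.108 = 22% for 1 to 9 months. This is the share for a comparison of means, and a guide to the rank test.

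**3. Power, plain v stratified by month on study (%).** Model A: count ~ Binomial(10, 1 − exp(−λt)), with λ = 0.05 (control) or 0.0575 (experimental) per item-month, times a gamma factor with variance 0.2. Where two runs differ, both values are shown. Model B: gamma-Poisson, dispersion 0.3, mean 3 × (t/6)^k, 1,500 replicates.

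| Months on study | A: near-constant adoption | B: linear (k = 1) | B: square root (k = 0.5) | B: flat (k = 0) |
|---|---|---|---|---|
| 6–9 | 83–84 v 84–86 | 78.1 v 79.3 | 76.5 v 77.2 | 74.7 v 74.5 |
| 3–9 | 72 v 78–79 | 70.1 v 74.5 | 71.5 v 72.0 | 75.6 v 74.9 |
| 1–9 | 55 v 70 | 55.5 v 68.9 | 68.8 v 71.7 | 76.2 v 75.6 |

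At 3 to 9 months the loss runs from nil (flat) through 0.5 and 4.4 points to 6–7 points. When the count is flat, stratifying costs under 1 point.

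**4. False-positive rate with no true effect** (model B unless stated; simulation error about √(0.05 × 0.95/1500) = 0.6 points).
- Everyone responds: plain test 4.5% to 6.3% across all windows and growth patterns.
- Response falls equally in both arms, 90% to 54% over 3 to 9 months: 5.2% and 5.8%; responders' mean time is 5.75 months in each arm.
- Response falls 2 points per month in control and an extra 2, 4 or 6 in experimental, 3 to 9 months. Linear growth: plain 6.5%, 8.5%, 12.5%; stratified 4.9% to 5.3%. Square-root growth: plain 4.3%, 5.0%, 6.6%. In the steepest case month-9 response is 0.90 − 0.08 × 6 = 42% v 0.90 − 0.02 × 6 = 78%.
- Model A, response 0.9 − 0.05t (experimental) v 0.9 − 0.025t (control): plain 7.6% to 8.5% at 3 to 9 months; 5.3% plain v 5.5% stratified at 6 to 9 months.

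Inflation therefore needs both a count that grows clearly with time and a response pattern that differs by arm.

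**The case against.** The strongest reply is that an unadjusted rank sum test in a randomised trial is valid, and that choosing a stratified version is a refinement often left to an analysis plan. The first half stands in full. The second stands in part: the article itself names both the test and the timepoint, so this is not a missing detail, but the change is a refinement and not a repair.

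Three further points carry weight.

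- **Window.** The Control section asks each participant for a diary week in the third month. On its natural reading everyone is followed into about month three, so the 1-to-9-month results should not be the headline.
- **Growth.** The experimental arm gets the education video and the app invitation at baseline. Changes may come early and then level off, in which case almost nothing is lost.
- **Estimand.** An effect averaged over the enrolment mix is a legitimate target for what the Discussion calls an operational trial. It is not an error.

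A reader might go further and infer that unequal time on study biases the comparison. The documents do not support that. One computer program randomises, and no change of ratio over time is described, so expected time on study is the same in both arms. The statement that "we weighted assignment to the experimental group 1.3 to 1 to ensure equal enrollment in each group" shows that the authors expected uneven loss during enrolment; it says nothing about questionnaire return months later. Incentives and reminders are described alike for both arms. If responders' time on study did differ by arm, that would be an imbalance in a recorded covariate, which the regression fallback could cover although it does not name time on study.

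**Conclusion.** The point holds as one of efficiency. Time to the closing form varies with enrolment date, the count is cumulative, and the named test ignores time. With 500 per arm, 3 to 9 months on study and a 15% higher experimental rate or mean, the cost is about 0 to 7 points of power: near zero if counts level off early, 4 to 7 if they keep growing roughly in proportion to time. Losses of 13 to 15 points appear only with steady growth and some participants having as little as one month. The size rests on an assumed enrolment window and growth pattern, neither of which the article gives.

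The planned test is not invalid. A distorted false-positive rate needs questionnaire response over time to differ between arms; this is possible but not shown.

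**What to change.** In the Statistical plan, replace the plain rank sum test on the end-of-study count with a rank sum test stratified by month of enrolment (van Elteren), or a regression that includes time since randomisation. Specify it in advance, independent of any observed imbalance.

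As a supportive analysis, report the comparison at a set month since randomisation that all participants can reach, using the monthly forms, on which sleep behaviour is also evaluated. The timing would be approximate: forms go out on the 28th, so the same numbered form can differ by up to about a month between participants.

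The cost is a line or two of text. No new data are needed, since the enrolment date and the monthly responses are already collected, and little is lost if the count turns out not to depend on time.
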